### Randomization and blinding procedures

2.4

Randomization will be performed by stratified block randomization method in treatment groups 1 and 2 and control group at a ratio of 1:1:1 to ensure a balanced distribution of the 3 groups. Subjects who meet all registration criteria will be randomly assigned to a randomization identification code (e.g., PLI-R-001, PLI-R-002, …, PLI-R-030) in the order generated by a computer randomization program. The randomization number will be given to each participant, and it will indicate whether PL 1000, 2000, or placebo is to be given. As this pilot study is designed to be double-blinded, the participants, researchers, and assessors collecting the data will be blinded to the group allocation. Information about intervention assignment will be stored in the third statistical department. The randomization code will be placed in an opaque envelope and stored at the hospital. With the exception of disclosure to individual patients with serious adverse events (SAE), randomization and blinding will not be disclosed to researchers until the end of the trial.

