### Outcome measures

2.6

The primary outcome is NK cell activity, which will be used to assess immune reactivity. The secondary outcomes are peripheral WBC count; levels of TNF-α, IFN-γ, IL-1β, IL-2, IL-6, and IL-12 to assess autoimmune reactivity; and levels of IgG1, IgG2, and IgM to assess allergic activity. URI symptoms will also be recorded. All outcome measures will be observed at every visit. For the safety of the participants, we will conduct laboratory tests, such as liver function panels, complete blood counts, and electrolyte levels, and we will evaluate vital signs. Safety assessments will be conducted at the second and third visits. Participants’ data will be anonymized and coded by a specific program.

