### Statistical analysis

2.8

Statistical analysis will be performed using the principle of full analysis set. For intention-to-treat (ITT) analysis, missing values will be analyzed by last observation carried forward (LOCF). The baseline values before treatment and the changes in NK cell activity at 4 weeks and after treatment will be measured for the 2 experimental groups and the control group. If the data follow a normal distribution, an independent *t* test will be performed to test the differences between 2 groups of continuous variables. If not, Mann–Whitney *U* test will be performed. Paired *t* tests will be performed to test the differences between groups if the data follow a normal distribution. If not, Wilcoxon signed-rank test will be performed. The test of normality for continuous variables will be analyzed using the Shapiro-Wilk test. The confidence level will be set at 5%. All statistical analyses will be performed using SPSS Statistics for Windows Version 20.0 (IBM Corp., Armonk, NY).

Drinking alcohol, which can affect the weekly evaluation, is considered a management variable, and if there is a difference between groups, an analysis of covariance (ANCOVA) will be performed. Descriptive statistics, such as number of subjects, mean, standard deviation, minimum, median, and maximum will be presented for baseline, at each visit, and at final evaluation. Change from baseline to final evaluation will be reported for continuous data, clinical laboratory tests, and vital signs. For categorical data, a division table will be provided. If necessary, 95% confidence intervals will be calculated. No intermediate analysis will be performed.

Demographic variables measured during the screening period will be summarized for each treatment group. Assays for comparison of drug administration groups will be performed. For this purpose, the continuous data will be tested using the *t* test or Wilcoxon rank-sum test. Categorical data will be analyzed using a chi-square test or Fisher exact test.

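### Baseline NK activity is measured in everyone but is a covariate in neither of the two primary analyses that the article names, which costs precision unless baseline and follow-up are very highly correlated

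*Protocol article*

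**What the plan says.** Section 2.6 (Outcome measures) fixes the endpoint, "The primary outcome is NK cell activity, which will be used to assess immune reactivity", and its timing: "All outcome measures will be observed at every visit". Section 2.8 (Statistical analysis) confirms that there is a pre-treatment value: it lists baseline values and says that "the changes in NK cell activity at 4 weeks and after treatment will be measured for the 2 experimental groups and the control group". For normally distributed data, "an independent *t* test will be performed to test the differences between 2 groups of continuous variables"; otherwise, "If not, Mann–Whitney *U* test will be performed". Neither test takes a covariate.

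Covariate adjustment appears once in section 2.8, for alcohol drinking: "if there is a difference between groups, an analysis of covariance (ANCOVA) will be performed". Baseline NK activity is not mentioned there.

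The Methods paragraph of the abstract assigns a different method to primary efficacy, a repeated-measures analysis on the full analysis set. It names no covariate, and section 2.8 does not mention this analysis.

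**The concern.** The pre-treatment value of the primary endpoint is usually among the best predictors of its later value, and here it is collected anyway. With 10 people per arm, chance differences between arms at baseline will often be sizeable. A change score subtracts the whole of such a difference, although only a fraction rho of it is expected to persist at follow-up, so it over-corrects. The results are a wider interval for the primary effect and, in the one trial actually run, an estimate that depends on which arm happened to start higher.

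The Discussion presents the trial as groundwork for further studies, so the precision of its effect estimate matters even though it is a pilot. Because the abstract and section 2.8 name different primary analyses, a reader also cannot tell which result will count as primary.

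**Working it through.** **The plan's own figure.** Section 2.3 takes 10 per group from a rule of thumb for pilot studies: 3 × 10 = 30, which agrees with section 2.1. The article states no power, SD or target difference, so there is no power figure to reproduce.

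**Inputs from the article.** n = 10 per arm, 1:1:1 (sections 2.1 and 2.3); 5% level (section 2.8).

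**Assumptions.** Two-sided test; equal SD s at baseline and follow-up; rho shown at 0.3, 0.5 and 0.7; effects of 0.5 SD (one reading of the medium effect in section 2.3) and 0.8 SD.

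**Step 1, variance.** The variance of a difference between two arms is V × 2/n, with (in units of s²):
- change score: V = 2(1-rho)
- ANCOVA: V = (1-rho²) × [1 + 1/(2n-4)] = (1-rho²) × 1.0625, where the second factor is the cost of estimating the slope from two groups of 10.

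The ratio ANCOVA/change score is therefore [(1+rho)/2] × 1.0625:
- rho 0.3: 0.65 × 1.0625 = 0.69
- rho 0.5: 0.75 × 1.0625 = 0.80
- rho 0.7: 0.85 × 1.0625 = 0.90

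Put the other way, the change-score variance is larger by about 45%, 25% and 11%. Simulation with 20,000 replicates per value of rho gave ratios of 0.69, 0.80 and 0.89.

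**Step 2, break-even.** Setting the ratio to 1 gives 1 + rho = 2/1.0625, so rho = 0.88. A three-arm model has a slope cost of 1 + 1/25 = 1.04, so rho = 2/1.04 - 1 = 0.92.

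**Step 3, power.** Noncentral t with noncentrality d/sqrt(V × 2/n), on 18 degrees of freedom for the change score and 17 for ANCOVA. Example at rho 0.5 and d = 0.8:
- change score: V = 1, SE = sqrt(0.2) = 0.447, noncentrality 1.79, power 39.5%
- ANCOVA: V = 0.797, SE = 0.399, noncentrality 2.00, power 47.2%

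| rho | 0.8 SD: change score | 0.8 SD: ANCOVA | 0.5 SD: change score | 0.5 SD: ANCOVA |
|---|---|---|---|---|
| 0.3 | 29.9% | 40.4% | 14.6% | 18.9% |
| 0.5 | 39.5% | 47.2% | 18.5% | 21.9% |
| 0.7 | 58.9% | 63.0% | 27.7% | 30.0% |

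Both columns of each pair use the same two arms, so none of the gain comes from pooling a third.

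**Step 4, chance imbalance.** The SD of a baseline mean difference between two arms is sqrt(2/10) = 0.45 baseline SD. A difference above 0.5 SD in either direction has probability of about 26% per pair of arms. Given a baseline difference D, the change-score estimate is shifted by -(1-rho) × D: for D = 0.45 SD and rho 0.5, by about 0.22 SD in the opposite direction. The simulated slopes of the estimate on D were -0.71, -0.51 and -0.31 for the change score at rho 0.3, 0.5 and 0.7, and about -0.01 for ANCOVA. Averaged over randomizations, neither estimate showed bias.

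**Step 5, does the abstract's analysis avoid this?** No baseline covariate is named there. In a conventional repeated-measures ANOVA with baseline as one of the time levels, the group-by-time contrast of baseline against a later visit is the same change-score comparison.

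**The case against.** The strongest defence is that this is a choice about precision, not an error. Under randomization the change-score comparison is valid and unbiased, and the article calls the trial a pilot and claims no power. All of that stands. A reader might infer that the planned analysis is biased. It is not, on average over randomizations; the shift in step 4 is conditional on the imbalance that happens to occur.

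Second, section 2.8 is not the only statement of the primary method, and it does not expressly tie the t test to the changes. This also stands. The change score is the natural reading, but a test of raw follow-up values would be unadjusted too, and the abstract's method adds no baseline covariate. The disagreement between the two passages becomes part of the point.

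Third, the size is easy to overstate. The large-sample ratio of 0.75 at rho 0.5 suggests 33% more participants for equal precision (1/0.75), but at 10 per arm the figure is about 25% for two groups and 28% for a three-arm model (1/0.78). Power gains that also include pooling three arms would not be due to baseline adjustment alone. Since rho is unknown, the gain could be negligible.

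Finally, section 2.4 says "Randomization will be performed by stratified block randomization method in treatment groups 1 and 2 and control group", and a reader might infer that a stratification factor has wrongly been left out of the model. The article names no factor, and a condensed article may leave both the factor and its use to the full protocol. That inference is not supported.

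**Conclusion.** The point holds as a worthwhile improvement, not as a flaw that invalidates the trial. Neither named analysis adjusts for baseline NK activity, and the abstract and section 2.8 disagree on which analysis is primary. Under equal SDs and rho between 0.3 and 0.7, adjustment removes roughly 31% to 10% of the variance of the primary comparison and adds about 10 to 4 percentage points of power at 0.8 SD, or about 4 to 2 points at 0.5 SD. It also takes out the dependence on chance baseline differences. The gain is gone at rho of about 0.88 for two groups and 0.92 for three. Adjustment does not make the pilot confirmatory: at 0.5 SD and rho up to 0.7, two-group power stays at or below about 30%.

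**What to change.** In section 2.8 and in the abstract, name the same single primary analysis: NK activity at week 8 by ANCOVA, or a repeated-measures model of the post-baseline visits, with baseline NK activity as a prespecified covariate and all three arms in one model. The adjustment should not depend on whether a baseline difference is seen. In place of the Mann–Whitney branch, state that a transformation or a rank-based ANCOVA will be used if residuals are clearly non-normal. Treat the continuous secondary outcomes (WBC count, cytokines, immunoglobulins) the same way, each with its own baseline.

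The cost is a few sentences and one degree of freedom per model. No new data are needed, because section 2.6 already has every outcome measured at every visit, and ANCOVA is already among the planned methods. The downside is no gain, or a very slight loss, if rho is about 0.9 or higher: at rho 0.9 the two-group variance ratio is 0.95 × 1.0625 = 1.01.

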**Methods::**

This study will be a single-center, randomized, double-blinded, and placebo-controlled trial. Study participants will be randomly allocated to 3 experimental groups: those taking PL 1000 mg, PL 2000 mg, or placebo. Total duration of the clinical trial will be 8 to 10 weeks. Study participants will have follow-up visits every 4 weeks and the effect and safety will be assessed at the second and third visits. All participants will be asked to maintain a dosage schedule for this protocol. The primary outcome will be natural killer (NK) cell activity and the secondary outcomes will include peripheral white blood cell (WBC) count; levels of tumor necrosis factor (TNF)-α, interferon (IFN)-γ, and interleukin (IL)-1β, IL-2, IL-6, and IL-12 to assess autoimmune reactivity; and levels of immunoglobulin (Ig)G1, IgG2, and Immunoglobulin M (IgM) to assess allergic activity. Repeated measure analysis will be used to measure primary efficacy based on full analysis set.

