### Study design

2.1

This study has been designed as a double-blinded, single-center, randomized clinical trial for investigating the efficacy of PL in immune functions. A total of 30 subjects with reduced immunity will be recruited from outpatients at DUCKMH through advertisements posted on bulletin boards at hospitals and apartments. Recruitment commenced in October 2019 and the trial is expected to end in December 2020. All participants will receive a full written explanation of the study's protocol and an informed consent form.

During screening, medical history within the past 6 months and drugs taken within the past 4 weeks will be recorded. Additionally, blood tests for liver function, complete blood count, and immune function will be performed.

A total of 30 adults with reduced immunity who meet the eligibility criteria for this study will be randomly assigned in a 1:1:1 ratio to treatment group 1 (PL 1000 mg), treatment group 2 (PL 2000 mg), or control group (placebo). The intervention will begin within 2 weeks of the screening visit.

Based on their study group, the subjects will be administered PL 1000 mg, PL 2000 mg, or placebo for 8 weeks. The total duration of the clinical trial will be 8 to 10 weeks. Subjects will have follow-up visits every 4 weeks, and the efficacy and the safety will be assessed at the second and third visits. The study flow chart is presented in Fig. 1.

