### Sample size calculation

2.3

We have demonstrated in both in vitro and in vivo experiments that PL has immunological effects. To determine the minimum effective concentration, PL was administered at various concentrations, and 200 and 400 mg/kg of PL was administered to mice for 7 days. Based on the United States Food and Drug Administration (FDA)'s guidelines for calculating the effective dose in humans, we used body surface area to translate the effective dose in animal studies to human studies. Based on these calculations, the effective dose in the human body was set at 960 and 1920 mg. For ease of production and intake, the dose was set at 1000 and 2000 mg. According to Whitehead et al^[13]^ in preliminary parallel-designed studies when effect size is considered medium, the empirically optimal sample size is 10 persons per group, due to considerations of feasibility, estimated average, and dispersion accuracy. Therefore, we designed a pilot study with 10 subjects in each group.

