## Discussion

3

The immune system is an organization of cells and molecules with specialized roles in defending against infection. Innate responses occur regardless of how many times the infectious agent is encountered, whereas adaptive responses continually improve with repeated exposure to a given infection. The innate responses use phagocytic cells (i.e., neutrophils, monocytes, and macrophages) that release inflammatory mediators (i.e., basophils, mast cells, and eosinophils), and NK cells.^[14]^

NK cells are effector lymphocytes of innate immunity endowed with constitutive cytolytic functions. Moreover, NK cells also show efficacy against assaults like viral infections and tumor development.^[15]^ It is important to include assays of NK cell markers, peripheral WBCs, TNF-α, IFN-γ, IL-1β, IL-2, IL-6, IL-12 as immunological biomarkers, as well as IgG1, IgG2, and IgM as allergic biomarkers.

In previous studies, PL has been shown to have anticancer effects through stimulating immune function. This study is the first to be conducted that will determine the appropriate dosage and duration of PL administration in human subjects. Although our sample size is small, and resultant biases may occur, this study may provide valuable insights into the mechanisms underlying the immune-stimulating effects of PL and will lay the foundation for further studies on the effect of PL on symptoms in patients with immune problems.

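### Section 2.8 gives only two-group tests with the pairs unnamed; nothing specifies a three-arm model or a direct comparison of the two doses, though the Discussion promises a dosage conclusion

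*Protocol article*

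**What the plan says.** All references are to the Protocol article. Sections 2.1 and 2.3 set three arms (placebo, 1000 mg, 2000 mg), 1:1:1, 10 per arm. The size comes from a pilot-study rule of thumb, which section 2.3 justifies as "due to considerations of feasibility, estimated average, and dispersion accuracy".

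Section 2.8 compares continuous variables between arms with an independent t test, or Mann-Whitney if normality fails: a "test will be performed to test the differences between 2 groups of continuous variables". It does not say which two groups. Two-group tests recur there for demographics, and again for the safety data. An ANCOVA is run only if alcohol drinking differs between groups.

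The Methods paragraph of the abstract says something else: "Repeated measure analysis will be used to measure primary efficacy based on full analysis set". Section 2.8 contains no such analysis, and the abstract gives neither its model nor how dose enters it.

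The Discussion states: "This study is the first to be conducted that will determine the appropriate dosage and duration of PL administration in human subjects".

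**The concern.** The arms are ordered doses of one product, and the article announces a conclusion about dosage. That conclusion needs an estimate of how the two doses differ, and none is specified. With two-group tests and unnamed pairs, the results most readily to hand would be each dose against placebo. Finding one dose significant and the other not does not show that the doses differ, and with 10 per arm that pattern arises often by chance. At stake is a dose preference carried into the next trial when the two doses in fact work equally well.

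The primary analysis is also not fixed: the abstract and section 2.8 name different methods.

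**Working it through.** **Inputs.** From the article: three arms, 10 per arm, 5% level (section 2.8 words it as a confidence level). Assumed, because the article gives no figure: two-sided tests, normal outcome with SD = 1 in every arm, complete data, and effects expressed in SD units. The only stated size is 3 × 10 = 30, which agrees. It has no power inputs behind it, so no power calculation can reproduce it.

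**1. What the passages cover.**
- Section 2.8: two-group tests; pairs unnamed; ANCOVA conditional on alcohol use.
- Abstract: repeated measures for primary efficacy; no model, no dose term.
- Discussion: a dosage conclusion.
- Nowhere: a specified three-arm model, a dose contrast, or the 2000 against 1000 mg difference.

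**2. Precision.** 95% CI half-width = t quantile × √(contrast variance).
- Two-group test, 18 df: 2.101 × √(1/10 + 1/10) = 2.101 × 0.447 = 0.94 SD.
- Same contrast from a three-arm model, 27 df: 2.052 × 0.447 = 0.92 SD.
- Mean of both doses against placebo: variance 1/10 + ¼(1/10 + 1/10) = 0.15, so 2.052 × 0.387 = 0.79 SD.

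**3. Power of one pairwise contrast** (noncentral t, noncentrality d/0.447):

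| d (SD) | 18 df | 27 df |
|---|---|---|
| 0.5 | 18.5% | 19.0% |
| 0.8 | 39.5% | 40.7% |
| 1.0 | 56.2% | 57.8% |
| 1.3 | 78.5% | 80.0% |

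Pooling all three arms adds at most about 1.6 points.

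**4. False dose preference.** Let both doses have the same true effect, 0.8 SD. Each reaches p<0.05 against placebo with probability 0.395, and

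P(exactly one) = 2 × [P(one given dose) − P(both)].

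If the two tests were independent, this would be 2 × 0.395 × 0.605 = 0.48. They share the placebo arm, so they are positively correlated. Simulation gives about 0.32, which implies P(both) = 0.395 − 0.16 = 0.235. At 0.5 SD the figure is 22%. A direct 5% test of 2000 against 1000 mg is wrong in 5% of such trials, by construction. Since pooling barely moves pairwise power (step 3), the remedy for the 32% is the direct comparison; a larger error df alone would not supply it.

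**5. Other contrasts.**
- Linear slope: with equal arms at 0, 1000 and 2000 mg the least-squares weights are −0.0005, 0, +0.0005. The slope is the 2000 mg minus placebo difference divided by 2000, so it adds nothing new.
- Mean of doses against placebo: if both doses are equal, power is 51.3% against 39.5% for one pairwise test at 0.8 SD, and 70.2% against 56.2% at 1.0 SD. If only 2000 mg works, at 1.0 SD, it is 24% against 56%.

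**6. SD for the next trial.** Chi-square 95% limits are ×0.69 to ×1.83 from one arm (9 df) and ×0.79 to ×1.36 pooled over three (27 df).

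**The case against.** Four points on the other side have force.

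- **The plan is not confined to pairwise tests.** The repeated measures analysis in the abstract and the conditional ANCOVA could each include all three arms. This stands. Neither is described as comparing doses, though, so the gap remains.
- **Testing pairs separately costs little.** A reader might infer that leaving out the third arm wastes much of the trial's precision. Steps 2 and 3 show that it does not. The 0.79 SD half-width answers another question (any PL against placebo), and its power gain depends on both doses working similarly. A joint two-contrast dose-response test is likewise a trade-off: if only 1000 mg works, at 0.8 SD, it has 15% power against 32% for Dunnett.
- **The article states no rule that the dose crossing p<0.05 is chosen.** Correct. Unnamed pairs do not exclude 2000 against 1000 mg, and the Discussion sentence belongs to a self-described pilot that admits its small sample. The 32% is therefore conditional on that reading.
- **The SD is not lost.** Section 2.8 tabulates n and SD. If these are given by arm, the pooled SD follows directly, and nothing says that a planner would use one arm alone.

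It can also be argued that contrasts belong in a fuller protocol or SAP that is not shown. That would excuse silence. Here section 2.8 positively names tests that do not match the three-arm design, the abstract names a different analysis, and the Discussion claims a conclusion that neither delivers.

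**Conclusion.** The point holds as a mismatch between the specified analysis and the stated dosage conclusion, together with an abstract and a methods section that disagree on the primary analysis. It should be corrected.

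The main consequence is the risk of a spurious dose preference: about 32% if dosage is read from significance against placebo, compared with 5% from a direct test. This assumes equal effects of 0.8 SD, 10 per arm, complete data and two-sided 5% tests; it is 22% at 0.5 SD.

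The documents do not support a claim of substantial lost precision or lost information on the SD, nor a claim that they commit to choosing the dose by its p-value against placebo.

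The corrected analysis will not settle dosage either. The direct dose difference has a half-width of 0.92 SD and, at a true difference of 0.5 SD, about 19% power. It would make that uncertainty visible.

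**What to change.** In section 2.8, replace the two-group tests by one model per outcome over all three arms, with residual variance from all 30 participants, and reconcile it with the repeated measures analysis named in the abstract so that both describe the same primary analysis. From that model report:

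1. each dose against placebo, with 95% CI;
2. the direct 2000 against 1000 mg difference, with 95% CI, as the only basis for any dosage statement;
3. the pooled residual SD, for planning the next trial.

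The mean of both doses against placebo may be added as a secondary estimate, with a note that it gains power only if both doses work similarly and loses it if only one does. A formal two-contrast dose-response test is not needed. Limit the dosage sentence in the Discussion to what the direct difference and its interval can show.

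The cost is wording and standard software, with no new data. The model assumes a common variance across arms, which can be checked and backed by an unequal-variance sensitivity analysis.

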The safety assessment will calculate the rate of adverse events. Continuous data, such as comparisons between groups, individual laboratory test results, and biomarkers will be analyzed using paired *t* tests or *t* tests with 95% confidence intervals within the group to see if there are any changes compared with the baseline. If normality is not met, nonparametric statistics (Wilcoxon signed-rank test or Wilcoxon rank-sum test) will be performed. Categorical data will suggest frequencies and ratios for each category. The difference between groups will be analyzed using chi-square test and Fisher exact test.

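### Section 2.8 assigns paired tests to differences between unmatched arms, contradicts its own independent-test rule, and leaves unclear which test decides NK cell activity

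*Protocol article*

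**What the plan says.** The Statistical analysis section (2.8) of the protocol article first states that, under normality, "an independent *t* test will be performed to test the differences between 2 groups of continuous variables". For non-normal data it adds: "If not, Mann–Whitney *U* test will be performed". The next sentence reads "Paired *t* tests will be performed to test the differences between groups if the data follow a normal distribution", and its fallback is "If not, Wilcoxon signed-rank test will be performed". Between-group differences are therefore given to two incompatible families of test.

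The safety paragraph of the same section begins "Continuous data, such as comparisons between groups, individual laboratory test results, and biomarkers will be analyzed using paired" and goes on to name paired or ordinary t tests, within the group, looking for change from baseline. One sentence thus covers both between-group comparisons and within-arm change.

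On design, Study design (2.1) allocates participants 1:1:1 to PL 1000 mg, PL 2000 mg or placebo, and no section defines matching. Sample size calculation (2.3) gives the arm size: "Therefore, we designed a pilot study with 10 subjects in each group". The Abstract names a repeated measures analysis for primary efficacy, which section 2.8 does not contain.

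**The concern.** A paired test needs a defined link between each observation in one set and one in the other. Participants in separately randomised arms have no such link, so the rule cannot be carried out without inventing one.

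The likely alternative meaning is before-after change within each arm. That is a proper use of a paired test, but it answers a different question: it uses no placebo data and cannot separate a product effect from anything that moves all arms together. Season is one candidate, since the trial runs from October 2019 to December 2020.

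What is at stake is which p-value is read as the answer on NK cell activity. Section 2.8 does not say which test decides the primary outcome, and the Abstract names a third method.

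**Working it through.** **Inputs from the protocol article.** Three unmatched arms (2.1); n = 10 per arm (2.3), and 3 × 10 = 30 agrees with the stated total; significance level 5% (2.8, where it is called a confidence level).

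**Assumptions.** Two-sided testing, normal data with unit SD, and the effect and drift sizes below. The documents give none of these. The figure of 10 per arm comes from a cited rule with no SD, power or numeric effect size, so no formula can reproduce it; the point does not depend on it.

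**1. Literal reading: paired test across arms**

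For a true difference of d SD, both tests have noncentrality d × √(n/2) = d × √5. The independent test has 18 degrees of freedom (critical t 2.101); the paired test on arbitrary pairs has 9 (critical t 2.262).

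| Assumed d | Noncentrality | Power, independent | Power, paired | Loss (points) |
|---|---|---|---|---|
| 0.5 | 1.118 | 18.5% | 17.1% | 1.5 |
| 1.0 | 2.236 | 56.2% | 51.4% | 4.8 |
| 1.3 | 2.907 | 78.5% | 73.5% | 5.0 |

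Losses are taken from unrounded powers.

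- Type I error in 200,000 simulated trials was 0.050 for the independent test and 0.049 for the paired test. Arbitrary pairing does not inflate it.
- The answer is not unique. In 20,000 simulated trials at d = 0.8, one random re-pairing of the same data changed the 5% decision in 14.2%.
- Pairing that depends on the data is a different matter. Lining up both arms by sorted value gave a type I error of 0.48.
- With 10 and 9 participants the test cannot be computed. Unequal arms are possible, because Withdrawal and dropout (2.9) excludes people who withdraw consent.

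**2. Alternative reading: paired test within each arm**

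Suppose PL has no effect and every arm shares a mean rise of m SD of change. The within-arm test has noncentrality m × √10 with 9 degrees of freedom. If p is the chance of a significant rise in one arm, the chance for at least one of the two PL arms is 1 − (1 − p)².

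| Assumed m | Noncentrality | p, one arm | At least one PL arm |
|---|---|---|---|
| 0.25 | 0.791 | 10.6% | 20% |
| 0.3 | 0.949 | 13.4% | 25% |
| 0.5 | 1.581 | 29.3% | 50% |
| 0.75 | 2.372 | 56.2% | 81% |
| 1.0 | 3.162 | 80.3% | 96% |

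For m = 0.5: 1 − (1 − 0.293)² = 1 − 0.500 = 0.50.

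Under the same conditions (simulated at m = 0.25 to 1.0), the independent test against placebo stayed at about 5% per contrast and about 9% for either of the two.

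**The case against.** The strongest reply is that this is a one-word slip. The independent t test and Mann–Whitney U come immediately before, the paired tests follow as the usual within-group counterpart, and the safety paragraph uses them against baseline. Nothing suggests that anyone intends to pair participants across arms. This is probably right, but the current sentence still says otherwise, and the safety paragraph mixes the two uses again instead of settling the matter.

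A reader might infer that the trial will present uncontrolled within-arm change as efficacy, so that the placebo comparison is lost. The documents do not support that. A valid between-group test remains prescribed, and no section makes within-arm change the efficacy criterion. The risk comes from the plan not saying which test decides.

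A reader might also infer a certain rise in false positives from the literal rule. With equal arms and a pairing that ignores the data there is none; the cost is power and an arbitrary answer.

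The drift sizes are fairly challenged too. NK cell activity is not an entry criterion. Selecting people with repeated upper respiratory infections would produce regression to the mean in it only as far as the two are correlated, and the documents give no such figure.

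**Conclusion.** The rule is wrong as written and should be corrected before analysis. Section 2.8 applies paired tests to independent arms and contradicts its preceding sentences.

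On the literal reading the damage is moderate: a power loss of about 1 to 5 points for assumed differences of 0.5 to 1.3 SD, a decision that one re-pairing reverses about 14% of the time at an assumed 0.8 SD, and no result at all with unequal arms.

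On the within-group reading the tests are legitimate as description but could mislead as evidence of effect. The 50% and 25% figures illustrate this for assumed shared changes of 0.5 and 0.3 SD; they are not forecasts for this trial. All figures assume normal data, two-sided 5% tests and 10 per arm.

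**What to change.** In both places in section 2.8 (the efficacy paragraph and the safety paragraph):

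- Limit the paired t and signed-rank tests to change from baseline within an arm. Label them descriptive and not a basis for an efficacy conclusion. A ban on within-arm p-values is not needed.
- State that efficacy and between-group laboratory comparisons rest on each PL arm versus placebo, reported with a 95% confidence interval.
- Name the analysis that decides NK cell activity and reconcile it with the repeated measures analysis in the Abstract.

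The cost is a few sentences of text. Data collection, sample size and trial conduct do not change.
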